### 3.6 Ethical considerations

The study will comply at all times with the principles of the European Code of Conduct for Research Integrity. Written consents will be obtained from all the participants. The University of Navarre Research Ethics Committee has approved this study (2021.204) and will monitor that the ethical principles of research involving human subjects are adhered to.

## 4. Preliminary results

The first edition of Care and Society took place from January to May 2022. The course had 29 students enrolled. For the preliminary results, we compared the PCKQ answers of the participants throughout the course. We also assessed the results of the Message Transmission Experiment, and we obtained an initial overview of the recurring themes of the focus group.

### 4.1 Palliative Care Knowledge Questionnaire

The students were asked to complete a PCKQ in three different moments of the course: before it started (Moment 1), after the first module (Moment 2), and during the last class (Moment 3). The PCKQ included four multiple choice questions with multiselect answer options, in which students were asked to pick the options that best described palliative care, and one open question in which students were asked to define palliative care. From the 25 students that accepted to participate, 12 students responded in Moment 1, 25 responded in Moment 2 and 21 responded in Moment 3.

The analysis carried out is centered on the open question and only took into consideration respondents who answered at the 3 Moments (S1 File). Although some of the students appear to have a vague knowledge on palliative care, when asked to define palliative care in Moment 1, the answers revolved around the idea of the final moments of the patient. The definitions made use of concepts such as “terminal”.

“The care and support received by terminally ill patients and their families”,P1.“It is a treatment that is carried out in very specific and extreme circumstances to provide the patient with a state of well-being and tranquility, avoiding the pain without cure”,P2.“Accompanying terminally ill people”,P3.

In Moment 2, we start to see a shift in perspective. While students still made use of words like “terminal” in the definitions, the answers were no longer focused on that topic. The ideas of reducing the pain and suffering, enhancing the life quality, and accompanying and caring for the patient were present in most of the answers.

“Palliative care is the support, help and assistance given to patients in advanced diseases with near-death expectation, so that they have a better quality of life and comfort, and their suffering is reduced”,P1.“Palliative care is a treatment for chronic illnesses or those with a life expectancy of less than 6 months, which helps the patient to reduce pain and give them a better quality of life”,P2.“Caring to reduce the suffering of a person who is terminally ill”,P3.

Finally, in the Moment 3, instead of asking for the definition one more time, the questionnaire included a variation of the same question: “What is the message you will carry with you regarding palliative care?”. The answers were very diverse, but a recurrent topic was the notion of palliative care as something people should have access to: “palliative care services are indispensable”, “everyone should have access to palliative care”, and “we all deserve to be cared for”. The PCKQ of Moment 3 also incorporated a new question: “Rate the need for training of future non-health professionals in the area of palliative care”. The possible answers were a scale that went from “very necessary” to “not necessary at all”. From the 21 respondents, 16 said rated palliative care knowledge as “very necessary”. 4 respondents said it was “necessary”. The only respondent left said it was both “necessary” and “very necessary”. Thus, by the end of the course, most of the students highly regarded the training they have received, and they valued it enough to consider it necessary for other students like them.

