#### 3.4.1 Moment 1: Initial assessment

In Moment 1, one week before the beginning of the course, students will receive an email inviting them to participate in the study. The invitation will have three links: one to the initial Palliative Care Knowledge Questionnaire (PCKQ), another to a Cognitive and Affective Empathy Test (TECA), and the last to a consent form for recontact. The initial PCKQ is meant to examine participants previous knowledge on palliative care. If any student shows a formidable knowledge on the topic, they will not be excluded from the study. Their performance will simply be recorded, and any improvement will be taken into consideration.

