## 6. Limitations

When launching the pilot, we decided not to have a control group. The two main reasons were: we did not consider the experience of a student taking Care and Society to be comparable to that of a student taking any other subject of the Core Curriculum offerings. And, secondly, the questionnaires themselves could lead to bias. By taking the same questionnaire repeatedly, it could generate curiosity in the control group participants, who might be able to acquire palliative care knowledge on their own and improve their performance in the following questionnaires. Nonetheless, for future attempts, we believe that the existence of a control group is advisable to rule out external change factors, such as exposure to news about the topic or to other media outlets.

The code system is another variable to take into consideration. As there is a time frame superior to a month in between moments of evaluation, some of the participants had a hard time remembering the city and the numbers they chose at the beginning of the pilot study. Furthermore, some of the participants chose the same city and the same combination of numbers. As a result, some of the answers had to be excluded from the preliminary results. In future attempts, a new system of codes might be helpful to improve the data recollection.

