## 7. Conclusions

The preliminary results of the pilot, delivered to 29 students from degrees not related to health sciences, suggest that the understanding of the students about palliative care changed and some of the common misconceptions were clarified. Additionally, the overall impressions of the experience were positive. Both students and professors enjoyed the approach of the course and found its content useful and valuable for their day-to-day life. After completing the course, some of the students appeared to be able to explain what palliative care is to guest students with little or no experience in the topic. Nonetheless, in future evaluations more work needs to be done in assessing the efficiency of the message transmission. A more accurate assessment of the recipients’ previous knowledge on the topic needs to be carried out.

Furthermore, to evaluate if these students became ambassadors of palliative care an in-depth analysis of the course material and the results of the mid-term assessment are required. Up to now, the results hint that: (1) the students have improved their knowledge on palliative care, (2) they share a positive attitude regarding palliative care, and (3) they have started to communicate palliative care to their peers. But the mid-term assessment will show more definite results in the previous three aspects. In addition, it will provide us with insights regarding the permanence of the learning and the initiative of the students to advocate for palliative care if faced with a situation in which palliative care is being wrongly depicted. Further analysis is also needed to evaluate if the course generates a change in the levels of empathy. Moreover, the benefits of the different education strategies used in this course need to be studied in more detail.

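### The reported knowledge comparison rests on at most 12 of 25 participants and on an open question replaced at Moment 3; the closed items and the analysed n are not reported

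*Protocol article*

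**What the plan says.** Section 4.1 of the protocol article describes the Palliative Care Knowledge Questionnaire (PCKQ) as four multiselect items plus one open question asking for a definition of palliative care. On response it states: "From the 25 students that accepted to participate", "12 students responded in Moment 1, 25 responded in Moment 2 and 21 responded in Moment 3". On the analysis it states: "The analysis carried out is centered on the open question and only took into consideration respondents who answered at the 3 Moments". It then describes how the definitions moved between Moments 1 and 2, with three students quoted at each.

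The same section says that at Moment 3 the definition was not requested again. Students were asked instead which message about palliative care they would take away. A new rating of the need for training was added and is reported for all 21 Moment 3 respondents. No result appears for the four multiselect items at any Moment.

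Section 6 adds that participants forgot or duplicated their self-made codes, so that "some of the answers had to be excluded from the preliminary results". The number excluded is not given.

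Section 4 reports that "The course had 29 students enrolled". The abstract's conclusion says without qualification that students' understanding changed. Section 7 says the results suggest this, for a pilot "delivered to 29 students from degrees not related to health sciences".

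**The concern.** Understanding of palliative care is the first of the four criteria by which section 3.4 defines an ambassador, so the knowledge comparison bears on the central question of the pilot. Three features weaken it together.

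- The restriction to students who answered at all three Moments caps the set at the number who answered at Moment 1, the smallest of the three.
- The restriction buys little. Like-for-like definitions exist only at Moments 1 and 2, so a Moment 3 answer is required without supplying a third comparable definition.
- The closed items, which could check the authors' reading of the free text, are not reported. That reading needs a check: all three definitions printed for Moment 2 still refer to nearness of death, short life expectancy or terminal illness. The article acknowledges that such words persisted and describes the shift without a count.

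A reader who meets 29 students in the conclusions, with no analysed n beside the claim, cannot see how narrow the base is or that it may be a selected part of the class. Section 6 discusses the missing control group and the code system. It does not mention the missing baselines. The project repeats the course and is meant for other universities (section 3.2), so the weakness could carry forward.

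**Working it through.** The article states no number of three-Moment respondents, so there is no stated figure to reproduce. The number can be bounded.

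**Inputs.** Enrolled: 29 (section 4). Accepted: 25. Respondents at Moments 1, 2 and 3: 12, 25 and 21 (section 4.1). Exclusions for codes: number not stated (section 6).

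**Size of the three-Moment set, before code exclusions**
- Upper bound: min(12, 25, 21) = 12.
- Lower bound among the 25 participants: 12 + 25 + 21 − 2 × 25 = 8. Since all 25 answered at Moment 2, this is the same as 12 + 21 − 25 = 8.
- Share of participants: 8/25 = 32% to 12/25 = 48%. Share of enrolled: 8/29 = 28% to 12/29 = 41%.

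**Questionnaires used**
- Total returned: 12 + 25 + 21 = 58.
- With 12 completers: 36 used, 22 unused, 22/58 = 38%.
- With 8 completers: 24 used, 34 unused, 34/58 = 59%.
- By Moment, the rule drops 0 to 4 of 12, 13 to 17 of 25, and 9 to 13 of 21.

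**Which bounds are firm.** Code exclusions can only shrink the set, so 12 is a firm ceiling and 38% a firm minimum for the unused share. The figures 8 and 59% are not firm limits. If exclusions left 5 completers, for example, 58 − 15 = 43 questionnaires would be unused, or 74%.

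**What the Moment 3 requirement costs.** All 25 participants answered at Moment 2, so each of the 12 Moment 1 respondents also has a Moment 2 definition. Before code losses there are 12 Moment 1 to Moment 2 pairs. Requiring a Moment 3 answer removes 0 to 4 of them (12 − 12 to 12 − 8) and adds no third definition.

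**What using all responses can and cannot do.** It makes up to 58 questionnaires available for summaries of the closed items by Moment. It creates no baselines: 25 − 12 = 13 participants have none, and comparisons from Moment 1 stay at 12 pairs or fewer.

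**The case against.** The strongest reply is that section 4 is headed as preliminary and describes what was done for a first look, not a fixed analysis rule. Section 7 uses guarded verbs and defers to the mid-term assessment and to an in-depth analysis of the course material. The article discloses the 12, 25 and 21, the restriction itself and the changed Moment 3 question. Following the same students through the course is a reasonable choice for a within-person narrative. The analysed n may also stand in supporting file S1, which section 4.1 cites and which is not shown here. All of this is fair and lowers the weight of the point. It does not remove it, because the article draws conclusions from this comparison and its text does not give the n.

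Several stronger readings are tempting but not supported:

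- **That the closed items have been abandoned.** The article says the analysis is centred on the open question and reports no closed-item result. It does not say they will never be analysed.
- **That e-mail collection caused the low baseline response.** Section 3.4.1 says that "one week before the beginning of the course, students will receive an email inviting them to participate in the study", and "12 students responded in Moment 1". But section 3.4.2 also has links sent to students for Moment 2, when all 25 responded. The delivery route therefore does not explain the shortfall, and an effect of timing is conjecture.
- **That the completers are the keenest students.** This is possible but untested.
- **That the restriction costs a calculable amount of statistical precision.** The reported comparison is a qualitative reading of free text, with no score, mean or standard deviation. Confidence-interval widths would describe no estimate in it. A comparison of Moments 2 and 3 could use more pairs but would say nothing about change from before the course.
- **That 29 is offered as the analysed number.** It is a true statement of how many students were enrolled. The fault is that no analysed number stands beside it.
- **That all other questionnaires were discarded.** The training-need rating uses all 21 Moment 3 respondents, so the unused share applies to the knowledge comparison only.

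**Conclusion.** The point holds as a moderate one. The reported knowledge comparison uses at most 12 of 25 participants and leaves at least 38% of the 58 questionnaires unused. Its Moment 3 requirement yields no comparable measurement. It is silent on the four closed items, while the abstract and section 7 draw a conclusion about changed understanding without the analysed n. The abstract is the more exposed of the two, because section 7 is hedged.

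The lower figure of 8 assumes that all respondents come from the 25 who accepted, as section 4.1 words it, and that no codes were lost. The ceiling of 12 needs neither assumption. That the closed items can be scored, and were the same at each Moment, is also an assumption: section 4.1 presents them as part of the questionnaire but shows no scoring key.

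**What to change.** - **Definitions.** Compare them over all linkable Moment 1 to Moment 2 pairs (at most 12), without requiring a Moment 3 answer. Report the Moment 3 answers separately, as responses to a different question.
- **Closed items.** Report the four multiselect items at each Moment on all usable responses, with a scoring key fixed before the answers are scored. Use paired comparisons where codes link and summaries by Moment where they do not. Keep the three-Moment completers as a sensitivity analysis.
- **Claims.** Put the analysed n beside each knowledge claim in the abstract's conclusion and in section 7, and qualify the abstract to match section 7.
- **Limitations.** State in section 6 that 13 of 25 participants have no baseline, that completers may be a selected group, and how many answers were excluded because of codes.
- **Later cycles.** Have the Moment 1 questionnaire completed in the first class, before any teaching, to raise baseline response.

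The cost is some re-analysis of data already held, edits to the text, and a little class time in each later cycle.

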#### 3.4.2 Moment 2: Learning assessment

Following the end of Module I, students will receive links to the PCKQ and TECA of Moment 2. Furthermore, to evaluate Module II for teaching purposes, a ten-minute debriefing will be recorded at the end of the Escape Room. With their written consent, transcripts of this recording will be used to help analyze the data.

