#### 3.4.3 Moment 3: Final assessment

The final two classes in the course contemplate a seminar where students will learn the basics of Rhetoric. They will write a speech, applying the knowledge of palliative care acquired during the course and the resources given throughout the seminar. The speeches will be sent to and graded by the professor, who will forward them to the research team to be analyzed accordingly. The teacher will then proceed to select the five best speeches for a Message Transmission Experiment. For this experiment, five selected students will deliver their speech in front of first-year students not enrolled or related in any way to the course. Following the speeches, the first-year students will fill out a questionnaire to assess their understanding of palliative care after the experience.

Additionally, prior to the last day of class, students will turn in a written reflection regarding the Module III experience. This material will also be analyzed for the research with the prior written consent of the students. After the class is over, students will receive the link to answer the last PCKQ and TECA. Participants will also receive a link to provide feedback on the course through a satisfaction and commitment questionnaire that includes an open question and a learning commitment regarding an attitude change: "After what you have learned in this course, what do you intend to change in your attitude in the coming months to enhance the palliative care message?".

Lastly, all the students and teachers of Care and Society will be invited to participate in a focus group to evaluate the overall experience in this course. The first five students who respond to this request will be selected. The purpose of this focus group is not to evaluate the knowledge of the participants, but to discuss the strengths and weaknesses of the methodology, the content and other aspects of the course. The focus groups will later be transcribed, and thematic content analysis of the material will be carried out.

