#### 3.4.4 Moment 4: Mid-term assessment

Five months after the publication of course grades, students will be emailed a link to an online questionnaire to assess their mid-term knowledge and to indicate the extent to which they have implemented the learning commitment outlined in the satisfaction and commitment questionnaire. Students should respond to the question “You have set out to change your attitude to improve the palliative care message. Have you managed to accomplish this in the last few months? Please provide an example.” Furthermore, they will receive an invitation to participate on in-depth interviews to talk about their experience on the months following the course and to confirm whether they have retransmitted the palliative care message at some point during that timeframe.

The 5-month timeframe was selected taking into consideration that the course grades will be made public in early June. Hence, we will be recontacting students no sooner than in November of 2022. Thus, by the time we recontact the students, some of them will be finishing their second-to-last semester in university. This is significant for two reasons. First and foremost, the recontact form they received in the Moment 1 of evaluation allowed communication via their university email. If we wait longer, some of the emails may become inoperative. Secondly, sending invitations with a semester’s leeway allows us to have plenty of time to schedule interviews knowing that the students are still in the same geographic location, facilitating face-to-face interviews or at least with similar schedules to ours.

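### The definition question that carries the reported knowledge analysis was replaced at Moment 3, so on that item understanding can be compared only before and after Module I

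*Protocol article*

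**What the plan says.** The Methods plan repeated use of one knowledge instrument. The PCKQ goes out one week before the course (section 3.4.1). It is sent again at Moment 2: "Following the end of Module I, students will receive links to the PCKQ and TECA of Moment 2" (section 3.4.2). At Moment 3, "students will receive the link to answer the last PCKQ and TECA" (section 3.4.3). Nothing in section 3.4.3 announces a changed item.

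Section 4.1 describes the content: "The PCKQ included four multiple choice questions with multiselect answer options", plus one open question asking for a definition of palliative care. It states that the reported analysis is centred on the open question and restricted to students who answered at all three moments. It then reports: "Finally, in the Moment 3, instead of asking for the definition one more time, the questionnaire included a variation of the same question". The replacement is given as "What is the message you will carry with you regarding palliative care". It mentions one other change at Moment 3, an added rating of the need for training.

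At Moment 4, "students will be emailed a link to an online questionnaire to assess their mid-term knowledge" (section 3.4.4); the items are not listed. Section 3.4 makes understanding of the concept, and retention of knowledge at five months, two of the four criteria for an ambassador. Section 7 says the results so far hint that "the students have improved their knowledge on palliative care". The conclusion of the abstract states without a hedge that understanding changed.

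**The concern.** A definition question asks what palliative care is. A take-home-message question asks what the student values about it. The misconception the course targets is the equation of palliative care with death or the end of life (section 1). Only a definition shows directly whether a student still holds it. The Moment 3 answers printed in section 4.1 concern access and entitlement to care, and a student could give any of them while still holding the misconception. Calling the new question a variation of the same one is therefore not accurate.

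At stake is what the only PCKQ comparison over time reported in the article can support. If the three moments are read as one series on one item, any difference between Moment 2 and Moment 3 mixes learning with the change of prompt. The escape room, service learning and rhetoric modules all fall after the last comparable definition.

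**Working it through.** The point is one of item comparability, so it rests mainly on setting the article's statements side by side. The only arithmetic is on response counts.

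**Step 1. Which item was asked when (sections 3.4 and 4.1).**

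| | Moment 1 | Moment 2 | Moment 3 | Moment 4 |
|---|---|---|---|---|
| Timing | before the course | after Module I | end of course | five months after grades |
| Open definition | asked | asked | replaced | not stated |
| Message question | no | no | asked | not stated |
| Four multiselect items | part of the PCKQ | part of the PCKQ | no change reported | not stated |
| Respondents | 12 | 25 | 21 | – |

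**Step 2. What the open item can compare.** Like-for-like definitions exist at Moments 1 and 2 only. Moment 2 follows Module I, so the contrast spans 1 of 4 modules; the other 4 − 1 = 3 come after it.

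**Step 3. How many students it rests on.** The analysis uses students who answered at all three moments. All 25 participants answered at Moment 2, so this set is the overlap of the 12 at Moment 1 and the 21 at Moment 3.

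- Smallest possible overlap: 12 + 21 − 25 = 8.
- Largest possible overlap: min(12, 21) = 12.

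The set is therefore 8 to 12 students before the exclusions for forgotten or duplicated codes described in section 6. How many were excluded is not given.

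**Step 4. What the printed answers show.** The three Moment 2 definitions in section 4.1 still refer to nearness to death, a short life expectancy or terminal illness, although the article reads them as less centred on that idea. The Moment 3 answers it quotes do not use that framing, but they answer a different prompt. The absence cannot be credited to the course.

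**Step 5. What the investigators used elsewhere.** In the Message Transmission Experiment (section 4.2), held in the last class, the two guests were asked to define palliative care, and those definitions served as the evidence of understanding. A definition was thus treated as a suitable measure for the guests at the point where the enrolled students' questionnaire left it out.

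**The case against.** The best case on the other side has four parts.

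- **The PCKQ has other items.** A reader might infer that no comparable measure of understanding exists at the end of the course. The article does not support that. The four multiselect items also ask what best describes palliative care, and the only changes reported at Moment 3 are the replaced open item and the added rating. They may give a comparison across Moments 1, 2 and 3. This stands, and it confines the point to the open item. It does not rescue the present conclusion, because no multiselect results are reported and the article does not say outright that these items were repeated unchanged.
- **Moment 4 is not described item by item.** A reader might infer that retention has no end-of-course reference at all. That is not established. If Moment 4 reuses the multiselect items, Moment 3 can be their reference, and a condensed article need not list every item. Only for the definition item is it certain that no Moment 3 value exists.
- **The article does not claim a shift in definitions at Moment 3.** The change in perspective is reported at Moment 2, on the identical item, and the closing inference for Moment 3 concerns how students value the training. The replacement is disclosed, and section 7 speaks only of hints, with firmer results expected from the mid-term assessment. All this stands. The abstract, however, drops the hedge, and neither conclusion says that the open-item evidence stops after Module I.
- **Modules II to IV have evidence of their own.** The plan includes the empathy test, a debriefing, reflections and speeches. They are therefore not unevaluated, but none of these supplies the missing definition.

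**Conclusion.** The point holds for the open definition item. It was asked at Moments 1 and 2 and replaced at Moment 3 by a question that does not measure the same thing. On the item that carries the reported knowledge analysis there is no comparable value after the full course. The valid contrast is Moment 1 versus Moment 2, spanning one module of four, in at most 12 students. A definition given at Moment 4 could be compared with Moments 1 and 2 but not with the end of the course.

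The size is moderate. This is a participatory pilot meant partly to improve its own assessment techniques (section 3.2), and the article defers the judgement on ambassador status. The verdict assumes that the description of the questionnaire in section 4.1 is complete. Whether the multiselect items were unchanged at Moment 3, and which items Moment 4 contains, cannot be settled from the article.

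**What to change.** 1. In later Teach-Inn Pal cycles, ask the identical definition question at all four moments. Keep the message question as an additional item placed after it, so that it cannot colour the definition.
2. For the pilot cohort, include the definition question in the Moment 4 form, which the article treats as still to come, and state that its comparators are Moments 1 and 2.
3. Confirm whether the four multiselect items were repeated unchanged at Moment 3. Where they were, report them as the Moment 1 to Moment 3 knowledge comparison.
4. In the abstract and section 7, limit the open-item conclusion on changed understanding to Moment 1 versus Moment 2, after Module I, and give the number of students analysed. In section 4.1, describe the Moment 3 question as a different question.

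The cost is one extra open item on an existing online form, the reporting of items the questionnaire already contains, and a narrower conclusion.

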### 3.4 Moments of evaluation

The evaluation will assess the capacity of the course to turn students into ambassadors that can change the framework of the discussion in society. We understand as ambassadors the students who demonstrate: (1) an adequate degree of understanding of the concept of palliative care, (2) a positive attitude towards the social problem, (3) the ability to communicate the message of palliative care and (4) to retain the knowledge five months after taking the course. The overall assessment of the course will focus on four moments of evaluation (Fig 3).

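### Attitude is an ambassador criterion but has no described pre-course measure, so the end-of-course attitude result cannot show a change due to the course

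*Protocol article*

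**What the plan says.** All references are to the protocol article.

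- **Aim and criterion.** Section 3.4 sets out to assess the course's capacity to make students into ambassadors. The second of four criteria is "a positive attitude towards the social problem".
- **Before the course.** Section 3.4.1 lists three Moment 1 links: the PCKQ, described as examining prior knowledge; the TECA, an empathy test; and a consent form for recontact. Section 4.1 describes the PCKQ as four multiselect questions on what palliative care is, plus an open definition.
- **After the course.** Section 4.1 reports: "The PCKQ of Moment 3 also incorporated a new question". It asked how necessary it is to train future non-health professionals in palliative care, on an ordered scale. Of 21 respondents, 16 chose very necessary, 4 chose necessary and 1 gave both.
- **Other attitude material.** Section 3.4.3 adds an open learning commitment on changing one's attitude. Section 3.4.4 asks at Moment 4 whether it was kept, with an example, and invites students to interviews.
- **What is concluded.** Section 4.1 infers that "by the end of the course, most of the students highly regarded the training they have received". Section 7 lists, among things the results hint at, that "they share a positive attitude regarding palliative care".
- **Design.** The course is an elective (section 3.3) and the pilot had no control group (section 6).

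**The concern.** The question in section 3.4 is about what the course produces. To speak to it, an attitude result needs a pre-course value or a comparison group, and here there is neither. Students who pick an elective on care may think such training necessary before the first class. A rating taken only at the end cannot separate that from an effect of teaching.

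A second problem is what the item measures. It asks about a need in general. A student could think such training very necessary and still judge this course poor. Section 4.1 nevertheless uses it as evidence of regard for the training received.

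This matters beyond the pilot. Section 3.2 presents the pilot as the chance to improve the course and its assessment techniques before use in other universities. If the gap is carried forward, criterion 2 will stay unassessable as a change throughout the three-year project.

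**Working it through.** **1. The article's count.** 16 + 4 + 1 = 21, which matches the 21 Moment 3 respondents in section 4.1.

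**2. Response.** Of the 25 who agreed to participate, 21/25 = 84.0% answered. Of the 29 enrolled, 21/29 = 72.4%.

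**3. The end-of-course result (Clopper-Pearson 95% intervals).**

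| Reading | Count | Proportion | 95% interval |
|---|---|---|---|
| Very necessary, double answer not counted | 16/21 | 76.2% | 52.8% to 91.8% |
| Very necessary, double answer counted | 17/21 | 81.0% | 58.1% to 94.6% |
| Necessary or very necessary | 21/21 | 100% | 83.9% to 100% |

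For 21/21 the lower limit is 0.025^(1/21) = 0.839. These figures describe the end of the course and contain no information about change.

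**4. What the missing baseline hides.** Suppose a proportion p would have answered favourably before the course and the course had no effect. Treating respondents as independent, the chance of 21 favourable answers out of 21 is p^21. The article gives no value of p, so the values below are assumptions.

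| Assumed p | p^21 |
|---|---|
| 80% | 0.9% |
| 90% | 10.9% |
| 95% | 34.1% |
| 98% | 65.4% |

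The same result is surprising or ordinary depending on a number that was never collected.

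**5. Does anything else supply a baseline?**

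| Source | Section | Before the course? |
|---|---|---|
| PCKQ at Moment 1 | 3.4.1, 4.1 | Yes, but described as knowledge |
| TECA at Moment 1 | 3.4.1 | Yes, but empathy |
| Training-need item | 4.1 | No, new at Moment 3 |
| Open take-home-message question | 4.1 | No, Moment 3 |
| Learning commitment | 3.4.3 | No |
| Follow-up of the commitment, interviews | 3.4.4 | No |
| Focus group | 4.3 | No |

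**6. What a baseline would have given in the pilot.** With 12 respondents at Moment 1 and 21 at Moment 3 among 25 participants, the number answering both is at least 12 + 21 − 25 = 8 and at most 12. That is before losses from forgotten or duplicated codes (section 6).

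**7. The construct.** Section 4.1 moves through three things: the need to train others (the question), a rating of palliative care knowledge ("From the 21 respondents, 16 said rated palliative care knowledge as" very necessary), and regard for the training received (the conclusion). Only the first was asked.

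**The case against.** The strongest reply is that the article does not claim an attitude change. Section 7 says knowledge improved, but only that students share a positive attitude; it calls both hints and defers to the mid-term assessment. Criterion 2 is worded as something students demonstrate, so an end-of-course measure can address it as a state. The plan also has a qualitative route to change: a commitment after the course and a check five months later, within participatory action research. Finally, this is a small pilot whose limitations section already advises a control group for later attempts.

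Much of this stands, and it rules out three stronger readings that a reader might infer:

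- *That the article asserts the course improved attitudes.* It does not say so outright; the causal element comes from the aim in section 3.4.
- *That the training-need item is the source of the section 7 statement.* The article never calls it an attitude item, and section 7 names no source. The open answers and focus-group notes may contribute, though these too are post-course.
- *That the double answer undermines the result.* It is 1 of 21, and all 21 are favourable however it is counted.

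The reply does not supply a pre-course value. The Moment 4 follow-up records self-reported change after the course. Section 6 mentions the control group and the codes but not the missing attitude baseline. The over-reading in section 4.1 remains even if no causal claim is intended.

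**Conclusion.** The point holds as a limit on what the attitude result can show. All 21 Moment 3 respondents, of 25 participants, rated training of this kind as necessary or very necessary. That is an end-of-course state in self-selected students without a control group. The change due to the course cannot be estimated: the data are compatible with anything from no change to a large one. Separately, section 4.1's conclusion that "most of the students highly regarded the training they have received" does not follow from the item.

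This rests on the instruments as the article describes them. If the full Moment 1 PCKQ held an attitude question that the article does not mention, a baseline might exist for that question, but not for the training-need item, which the article says was new. The section 7 wording is hedged and defensible as description; it should not be used as evidence that the course met criterion 2 by its own effect.

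**What to change.** **Pilot report (rewording only).**
- In section 4.1, state that all 21 Moment 3 respondents (of 25 participants) rated such training as necessary or very necessary, and that change is not assessable. Remove the inference about the training received.
- Take views on the training received from the satisfaction questionnaire in section 3.4.3.
- Add the missing attitude baseline to section 6, and describe the attitude statement in section 7 as an end-of-course observation.

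**Later editions and centres.**
- Ask the same attitude item at Moments 1, 3 and 4, with only one answer allowed, and report the paired shift.
- Raise Moment 1 response above the pilot's 12 of 25 and replace the code system, or there will be few pairs.
- Expect a ceiling: with every pilot answer necessary or very necessary, an item of this kind may show little movement even if attitudes change. An item with more room at the upper end may serve better.

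A look-back rating at Moment 4 could be kept as exploratory only. It is open to recall and desirability bias, which would have to be stated, and it does not replace a baseline.

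The cost is one closed item on existing online forms, plus the work on response and codes that the other repeated measures need anyway. A control group would still be needed to rule out outside influences, as section 6 recognises.
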